### Procedure

Caregiver-patient dyads recruited via the national ALS/PMA database will be contacted by telephone. In this telephone call, the dyad will receive information about the study. When dyads are interested in participating, the inclusion criteria will be checked. Eligible dyads receive the study information letter per postal mail. One week after sending the information letter, caregivers will be contacted by telephone. Caregivers who do not want to participate will be asked for their reasons for not participating and we will assess their burden of caregiving with the one item, Self-Rated Burden scale (SRB) [33].

Caregiver-patient dyads can find information about the research and can apply to participate on the Dutch ALS Center website. Thereafter, the researcher will send the research information letter. One week after sending the information letter, caregivers will be contacted by telephone to answer questions and to check the inclusion criteria.

Dyads are asked to return the signed informed consents by postal mail. Once the informed consents have been received, participants are sent an invitation via e-mail to fill out the first assessment (T0).

### Randomization

After completing the first assessment, dyads will be randomized into the wait-list control or experimental condition by the researchers according to a computerized programmed randomization scheme. Randomization will be stratified for the degree of functional impairment of the patient (Amyotrophic Lateral Sclerosis Functional Rating Scale-Revised, using the cut off score for severe disabilities ≥ 24) [34, 35], presence of behavioral problems of the patient (Amyotrophic Lateral Sclerosis-Frontotemporal Dementia-Questionnaire, using the cut off score for mild behavioral changes ≥ 22) [36] and gender of the caregiver.

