### Sample size

The sample size calculation was based on Hospital Anxiety Depression Scale (HADS) data of informal caregivers in a previously completed study [6]. The total number of caregiver-patient dyads needed to detect a clinically relevant difference [32] of 3.65 points, with a standard deviation of 7.3 between the groups at T2, with an alpha of 0.05 and a power of 80%, is 116 caregiver-patient dyads (58 dyads in each group). Taking into account an attrition rate of 20%, we aim to include 140 caregiver-patient dyads in total.

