### Assessments

All quantitative assessments are self-report measures and will be administered online. Overviews of the questionnaires for caregivers and patients and their time of assessment are provided in Tables 2 and 3. Participants who discontinue the intervention will be asked to complete study follow-up assessments. Semi-structured qualitative interviews will be conducted by telephone.

**Table 2 Tab2:** Measurement overview caregivers

		Measurement^a^			
Outcome	Instrument	T0	T1	T2	T3
*Socio-demographics*					
Caregiver, patient, and care characteristics	iMTA Valuation of Informal Care Questionnaire	x			
*Primary outcome*					
Psychological distress	Hospital Anxiety and Depression Scale	x	x	x	x
*Secondary outcomes*					
Quality of life	Care-related Quality of Life −7 + Care-related Quality of Life - VAS	x	x	x	x
Burden	Zarit Burden Interview + Self-Rated Burden scale	x	x	x	x
*Mediator*					
Self-efficacy	Revised scale for caregiving self-efficacy	x	x	x	x
*Covariates*					
Satisfaction with relationship	Satisfaction Questionnaire	x	x	x	x
Social Support	Multidimensional Scale of Perceived Social Support	x	x	x	x
Behavioral changes patient	Amyotrophic Lateral Sclerosis-Frontotemporal Dementia- Questionnaire	x	x	x	x
Physical functioning patient	Amyotrophic Lateral Sclerosis Functional Rating Scale- Revised	x	x	x	x
*Evaluation*					
Evaluation intervention	Client Satisfaction Questionnaire + Self developed scale		x^b^		x^c^

^a^T0 = Baseline, T1 = 3 months, T2 = 6 months, T3 = 9 months

^b^only for the intervention group

^c^only for the wait-list control group

**Table 3 Tab3:** Measurement overview patients

		Measurement^a^			
Outcome	Instrument	T0	T1	T2	T3
*Secondary outcomes*					
Quality of life	McGill Single Item Scale	x	x	x	x
Psychological distress	Hospital Anxiety and Depression Scale	x	x	x	x
*Covariates*					
Self-perceived as burden	Self-perceived Burden Scale - 1 item	x	x	x	x

^a^T0 = Baseline, T1 = 3 months, T2 = 6 months, T3 = 9 months

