### Analyses

#### Statistical analyses

Descriptive statistics will be used to report demographic variables, clinical outcomes, and the use of the different modules. Group differences in primary and secondary outcomes will be compared with linear mixed model analyses, in which the mediator and covariates will be included. Statistical analyses will be performed primarily according to intention-to-treat and secondarily according to per-protocol principles. The intention to treat analyses will include data of all included caregivers, regardless of their adherence to the intervention or their missing data. In the per-protocol analyses we will only include caregivers who completed at least 4 modules (66.7%) and the T2 measurement. All hypotheses will be tested 2-sided, with a critical value of 0.05. Effect sizes on the primary outcome variable (HADS total) will be calculated with Cohen’s D using the means and pooled standard deviations of the two groups.

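### The covariates named for the mixed model include neither caregiver gender, a stratification factor, nor T0 HADS, so nothing written secures the precision that baseline could give

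*Protocol article*

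**What the plan says.** Protocol article, Randomization: dyads are randomized after completing T0, within strata defined by an ALS-FRS-R cut-off, an ALS-FTD-Q cut-off "and gender of the caregiver".

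Protocol article, Statistical analyses: group differences are to be compared with linear mixed models "in which the mediator and covariates will be included". The section does not list the covariates. The word corresponds to a heading in Tables 2 and 3 and in the Assessments text. Under that heading stand relationship satisfaction, social support (the "Multidimensional Scale of Perceived Social Support"), ALS-FTD-Q and ALS-FRS-R for the caregiver, and one self-perceived burden item for the patient. All five are marked at T0, T1, T2 and T3.

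HADS is also marked at T0 to T3, but under the primary outcome. Caregiver characteristics come from a T0 questionnaire under socio-demographics. The article does not state whether T0 HADS is a response, a covariate, or unused.

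Protocol article, Sample size: the target is stated as "clinically relevant difference [32] of 3.65 points, with a standard deviation of 7.3 between the groups at T2". At 5% significance and 80% power the section arrives at 58 dyads per group and, after a 20% allowance for attrition, 140 to enrol. It uses no baseline correlation.

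**The concern.** T0 HADS is measured before randomization and is likely to be the strongest available predictor of T2 HADS. Using it properly narrows the confidence interval and removes the effect of a chance imbalance at T0. A mixed model does not do this automatically. If T0 is one more response with separate group means at every visit, the T2 contrast is essentially the raw T2 difference, and a chance T0 imbalance stays in it.

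Stratified randomization balances the arms on the strata. An analysis that leaves out a prognostic stratum does not take credit for that balance, and its standard error is somewhat too large. Gender is absent from the named covariates. The other two factors are present as instruments scored at four visits, which is not the same as the T0 categories used to randomize.

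At stake is precision in a trial whose power on its own inputs is below the stated 80%.

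**Working it through.** **Inputs.** Difference 3.65 and SD 7.3 (taken as the within-group SD), so a standardized difference of 0.50; 58 per group; 20% attrition; 140 enrolled (all Sample size). Two-sided 0.05 (Statistical analyses). The T0-T2 HADS correlation r is not given; I assume 0.3 to 0.6. The test-retest figures of .86 to .91 quoted for the HADS describe reliability, not a six-month correlation in these caregivers, so I do not use them.

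**The plan's own figure.** n per arm = 2 × (1.960 + 0.842)² / 0.50² = 62.8, so 63 per arm and 126 in total (t-based 63.77, so 64 and 128). The stated 116 is not reproduced; a one-sided test gives 50 to 51 per arm, so that does not explain it. Also, 140 is about 116 × 1.2, whereas 116 / 0.8 = 145.

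**Power without baseline.** 140 × 0.8 = 112, or 56 per arm. SE = 7.3 × √(2/56) = 1.380. Power = Φ(3.65/1.380 − 1.96) = 75.4% (t-based 74.6%). At 58 per arm it is 76.8% (t-based 76.1%).

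**Power with T0 HADS as covariate.** SE = 1.380 × √(1 − r²), 56 per arm:

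| assumed r | SE | power, normal | power, t-based |
|---|---|---|---|
| 0 | 1.380 | 75.4% | 74.6% |
| 0.3 | 1.316 | 79.2% | 78.5% |
| 0.4 | 1.264 | 82.3% | 81.6% |
| 0.5 | 1.195 | 86.3% | 85.7% |
| 0.6 | 1.104 | 91.1% | 90.6% |

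The r at which 80% is reached is √(1 − 56/62.8) = 0.33 (t-based √(1 − 56/63.77) = 0.35).

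**Does the way T0 enters matter?** With complete T0, T1 and T2 data, 56 per arm and equal correlations of 0.5:

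- T0 as a response with a common mean in both arms: SE 1.195, the same as with T0 as a covariate.
- T0 as a response with free group means, contrast at T2: SE 1.380, no gain.
- The same free-means model, contrast of change from T0 to T2: SE = 1.380 × √(2(1 − r)) = 1.380, again no gain. At r = 0.6 it is 1.234 (power 84.1%, against 91.1% for adjustment). At r = 0.3 it is 1.380 × √1.4 = 1.632, worse than ignoring baseline.

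**With attrition.** The free-means model also uses T0 from caregivers who miss T2. With 70 randomized and 56 observed per arm, the variance of a T2 mean is about (σ²/56)(1 − 0.2r²). At r = 0.5 that is a 5% reduction, against 25% (r²) for proper adjustment. So the gain is close to nothing, but not zero.

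**Gender.** If gender explains an assumed 1% to 5% of the T2 variance, power at 56 per arm goes from 75.4% to between 75.8% and 77.5%.

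**The case against.** The strongest reply is that this is a short analysis paragraph in a journal article, and that an SAP would normally say how baseline and the strata enter. Tables 2 and 3 are measurement schedules that place each instrument under one heading. HADS is already listed as the outcome and gender falls under socio-demographics, so neither would be repeated under covariates. The text also permits the common-baseline-mean model, in which no precision is lost.

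Much of this stands. A reader might infer that the plan discards baseline HADS and thereby gives up precision. The article does not say so; it leaves the question open. A reader might also infer that the strata are ignored. That holds in full only for gender, since the other two instruments are in the list, though not as T0 categories. Leaving out a stratum is conservative and does not bias a linear contrast. The 75% comparator is an unadjusted comparison of 112 completers, which is not the analysis planned.

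What remains is that the article does more than stay silent. It says that the covariates go into the model and heads a specific set of variables with that name, and that set does not match the article's own stratification factors or include T0 HADS. Calling the analysis a linear mixed model does not close the gap, because common versions of that model use baseline very differently.

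**Conclusion.** The point holds as a gap between the named covariates and the design. Gender and T0 HADS are not in the set, two strata are there only as repeated measures, and nothing written secures the gain from baseline. That gain is worth about 4 points of power at r = 0.3, 7 at r = 0.4 and 11 at r = 0.5, all at 56 per arm. These figures rest on an assumed r and on the SD of 7.3. At r = 0.3 power is still just under 80%.

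It would be tempting to blame the covariate list for the missing power. The documents do not support that: the shortfall arises in Sample size, from 116 where the stated inputs need 126 to 128, and from inflating by 1.2 rather than dividing by 0.8. Baseline adjustment is a remedy for the shortfall; its absence is not the cause. The case for gender rests on matching the randomization and getting correct standard errors, not on power.

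**What to change.** State the primary model in the protocol or SAP as HADS at T1 and T2 on group by categorical time, with T0 HADS and its interaction with time, and the three stratification factors as recorded at T0 (caregiver gender, ALS-FRS-R stratum, ALS-FTD-Q stratum) as fixed effects. A T0-T2 model with one common baseline mean for both arms, plus the same three factors, is an equivalent choice. Use the same form for each secondary outcome with its own T0 value.

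All these variables are collected before randomization, so no new data and no extra dyads are needed. The cost is wording and a few degrees of freedom. The sample-size figures need their own correction; this change does not replace it.

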### The intervention

The content of the support program for informal caregivers is based on an online intervention aimed at partners of patients with cancer [37, 38]. This intervention, based on ACT, was adapted to the specific needs of ALS caregivers. We interviewed 21 ALS caregivers about their support needs [17] and added information and exercises related to these needs to the support program. Next, we asked 6 ALS caregivers and professionals in ALS/PMA care and research (physicians, psychologists and researchers) to provide feedback on the content of the program. Based on their feedback, text materials were adjusted and the web-based application was developed. In a usability test, five partners were observed while using the web-based application and they were asked to evaluate it. Their feedback was used to improve the usability of the web-based application.

The support program consists of an introductory face-to-face appointment with a psychologist, 6 psychologist-guided online modules and one closing telephone contact with the psychologist. The total program can be completed in 8 weeks. If caregivers need more time due to personal circumstances, they have the opportunity to work through the total program in 12 weeks. The content of the support program, the topics and the goals of each part are presented in Table 1.

**Table 1 Tab1:** Content intervention

Part of intervention	Topics	Goals	Key components
Face-to-face session	• The care situation • Wellbeing caregiver • Information about support program • Log in online modules	To receive information about the care situation and establish a relationship between the psychologist and the caregiver. To inform about caregiver burden and start online modules.	• Psychoeducation
Online module 1 Coping with your emotions and thoughts	• Dealing with and expressing emotions • Recognizing thoughts	To recognize emotions and encourage caregivers to allow, express and share emotions that can arise. To recognize dysfunctional thoughts and rumination. Change the way the caregiver relates to thoughts/to create distance from thoughts.	• Acceptance • Cognitive defusion • Mindfulness
Online module 2 The art of communication	• Communication style • Communication about sensitive topics • Communication about providing care	To improve the overall communication and to communicate with the patient about sensitive topics and providing care in the future.	• Communicating about what really matters • Mindfulness
Online module 3 Your resilience plan	• Dealing with continuous stress • Moments of relaxation • Using your sources	To make a resilience plan that may allow caregivers to maintain health during this stressful period by taking care of themselves.	• Acceptance • Mindfulness
Online module 4 What is really important	• Values in relationship • Values in life	To identify the values of the caregiver in different areas of life and to plan action to meet these values.	• Values • Commited action • Mindfulness
Online module 5 Moments of joy	• Positivity during difficult times • Celebrate the relationship	To seek, enjoy and cherish the positive moments in the relationship and in life.	• Committed action • Mindfulness
Online module 6 A good last period	• Life story of the patient • Communication in this last phase • Beautiful memories • Being grateful	To create a beautiful last period with the loved ones and to make memories with the patient for the future.	• Acceptance • Communicating about what really matters • Committed action • Mindfulness
Telephone call	• Any questions • Finish the support program	To offer support with regard to any issues and close the support program.	

#### Face-to-face session

Participants will have a one-hour session with a psychologist before they start with the online modules at the residence of the caregiver. The session is protocolized: the psychologist briefly explains the purpose of the intervention, receives information about the caregiving situation, logs in and demonstrates the online program and establishes a working relationship with the participant. Following this session, the caregiver starts with the online modules.

#### Online modules

The online part consists of 6 online modules, each module is directed at a specific theme. All modules start with an introduction directed at the theme of the module, followed by psychological exercises. The content of the online modules is focused on the following key components: 1] acceptance (embracing the private events without unnecessary attempts to change them [39]), 2] values (identifying valued domains of life [40]), 3] committed action (actions to pursue one’s values [40]), 4] mindfulness (training conscious awareness and attention from one moment to the next moment [41]), 5] communication about what really matters, 6] cognitive defusion (change the way one interacts with or relates to thoughts by altering the contexts in which they occur [39]). Participants also receive practical information, tips and references to relevant websites, organizations and other sources of information and support associated with the theme of the module. They are able to get in contact with other participating caregivers of patients with ALS or PMA, using the online program. They have an online personal profile and can send each other private messages. Participants can also share tips and advice with fellow participants.

The same psychologist who visited the participant for the face-to-face session provides online feedback including feedback on the completed exercises, a reflection on the progress of the participant and a reaction to any questions or difficulties.

#### Telephone contact

The program ends with a telephone call with the psychologist. During this call, the caregiver can ask for advice for specific problems and discuss questions that came up after completing the last module.

#### Guidance

The support will be provided by psychologists who are trained to provide the intervention.

### Assessments

All quantitative assessments are self-report measures and will be administered online. Overviews of the questionnaires for caregivers and patients and their time of assessment are provided in Tables 2 and 3. Participants who discontinue the intervention will be asked to complete study follow-up assessments. Semi-structured qualitative interviews will be conducted by telephone.

**Table 2 Tab2:** Measurement overview caregivers

		Measurement^a^			
Outcome	Instrument	T0	T1	T2	T3
*Socio-demographics*					
Caregiver, patient, and care characteristics	iMTA Valuation of Informal Care Questionnaire	x			
*Primary outcome*					
Psychological distress	Hospital Anxiety and Depression Scale	x	x	x	x
*Secondary outcomes*					
Quality of life	Care-related Quality of Life −7 + Care-related Quality of Life - VAS	x	x	x	x
Burden	Zarit Burden Interview + Self-Rated Burden scale	x	x	x	x
*Mediator*					
Self-efficacy	Revised scale for caregiving self-efficacy	x	x	x	x
*Covariates*					
Satisfaction with relationship	Satisfaction Questionnaire	x	x	x	x
Social Support	Multidimensional Scale of Perceived Social Support	x	x	x	x
Behavioral changes patient	Amyotrophic Lateral Sclerosis-Frontotemporal Dementia- Questionnaire	x	x	x	x
Physical functioning patient	Amyotrophic Lateral Sclerosis Functional Rating Scale- Revised	x	x	x	x
*Evaluation*					
Evaluation intervention	Client Satisfaction Questionnaire + Self developed scale		x^b^		x^c^

^a^T0 = Baseline, T1 = 3 months, T2 = 6 months, T3 = 9 months

^b^only for the intervention group

^c^only for the wait-list control group

**Table 3 Tab3:** Measurement overview patients

		Measurement^a^			
Outcome	Instrument	T0	T1	T2	T3
*Secondary outcomes*					
Quality of life	McGill Single Item Scale	x	x	x	x
Psychological distress	Hospital Anxiety and Depression Scale	x	x	x	x
*Covariates*					
Self-perceived as burden	Self-perceived Burden Scale - 1 item	x	x	x	x

^a^T0 = Baseline, T1 = 3 months, T2 = 6 months, T3 = 9 months

#### Primary outcomes measure

##### Caregivers’ psychological distress

Psychological distress will be measured using the HADS [42, 43]. This scale consists of 14 items reflecting symptoms of anxiety and depression by 7 items each. Items are scored on a 4-point scale and total scores range from 0 to 42. Furthermore, a total score for the subscales depression and anxiety can be calculated. The internal consistency for the total scale and both subscales is sufficient to high (Cronbach’s alpha ranging from .71 to .90). The test-retest reliability for the total scale and both subscales proved to be high (correlation coefficient ranging from .86 to .91) [42, 44].

#### Secondary outcomes measures

##### Caregiver burden

The Zarit Burden Interview (ZBI) will be used to measure caregiver burden by evaluating disease impact on caregivers’ quality of life, psychological suffering and impact on social and family relationships [45]. We will use a short version of 12 items, which has shown to have comparable psychometric properties to the full version that consists of 22 items [46]. The ZBI contains a 0–4 point scoring system with the following answering options: never, rarely, sometimes, quite frequently and nearly always. The questionnaire yields a maximum score of 48. A score ≥ 17 indicates a high burden. The ZBI short form shows good validity, internal consistency, and discriminative ability [47].

Burden of caregiving will additionally be measured with the Self-Rated Burden scale (SRB) [33]. The SRB is a single question in which informal caregivers are asked to give an overall assessment of the burden they experience from caring by using a visual analogue scale. The scores range between ‘0’ (not at all straining) and ‘10’ (much too straining). The SRB is a valid and reliable question and it can be used for a quick screening of caregivers at risk [33].

##### Caregivers' quality of life

Caregivers’ quality of life will be assessed using the Care-related Quality of Life (CarerQoL) [48]. The CarerQoL combines a description of the burden of caregiving on seven care dimensions (CarerQoL-7) with a valuation component (CarerQoL-VAS) assessing general quality of life in terms of happiness. The CarerQoL-7 provides answering categories ‘none’ (1), ‘some’ (2), and ‘many’ (3). The CarerQoL-VAS contains 0, ‘completely unhappy’ and 10 ‘completely happy’ as endpoints. The psychometric properties of the CarerQol were shown to be satisfactory [48–50].

##### Patients’ quality of life

Patients’ self-rated quality of life will be measured using the McGill Quality of Life Questionnaire (MQOL) [51], which is designed to measure the quality of life of patients with a terminal illness. In order to burden the patients as little as possible, we will only use the single item scale which assesses the overall quality of life with answer scores ranging from 0 = very bad to 10 = excellent.

